## Abstract

**Background:**

Sepsis is triggered by an infection and represents one of the greatest challenges of modern intensive care medicine. With regard to a targeted antimicrobial treatment strategy, the earliest possible pathogen detection is of crucial importance. Until now, culture-based detection methods represent the diagnostic gold standard, although they are characterized by numerous limitations. Culture-independent molecular diagnostic procedures represent a promising alternative. In particular, the plasmatic detection of circulating, cell-free DNA by next-generation sequencing (NGS) has shown to be suitable for identifying disease-causing pathogens in patients with bloodstream infections.

**Methods:**

The *DigiSep-Trial* is a randomized, controlled, interventional, open-label, multicenter trial characterizing the effect of the combination of NGS-based digital precision diagnostics with standard-of-care microbiological analyses compared to solely standard-of-care microbiological analyses in the clinical picture of sepsis/septic shock. Additional anti-infective expert consultations are provided for both study groups. In 410 patients (*n* = 205 per arm) with sepsis/septic shock, the study examines whether the so-called DOOR-RADAR (Desirability of Outcome Ranking/Response Adjusted for Duration of Antibiotic Risk) score (representing a combined endpoint including the criteria (1) intensive/intermediate care unit length of stay, (2) consumption of antibiotics, (3) mortality, and (4) acute kidney injury (AKI)) can be improved by an additional NGS-based diagnostic concept. We also aim to investigate the cost-effectiveness of this new diagnostic procedure. It is postulated that intensive/intermediate care unit length of stay, mortality rate, incidence of AKI, the duration of antimicrobial therapy as well as the costs caused by complications and outpatient aftercare can be reduced. Moreover, a significant improvement in patient’s quality of life is expected.

**Discussion:**

The authors´ previous work suggests that NGS-based diagnostics have a higher specificity and sensitivity compared to standard-of-care microbiological analyses for detecting bloodstream infections. In combination with the here presented *DigiSep*-Trial, this work provides the optimal basis to establish a new NGS-driven concept as part of the national standard based on the best possible evidence.

**Trial registrations:**

DRKS-ID DRKS00022782. Registered on August 25, 2020

ClinicalTrials.govNCT04571801. Registered October 1, 2020

**Supplementary Information:**

The online version contains supplementary material available at 10.1186/s13063-021-05667-x.

## Background

With an annual global incidence of nearly 50 million cases and up to 11 million deaths per year (accounting for 20% of total mortality worldwide), sepsis remains an ongoing challenge in intensive care medicine [1]. Sepsis is defined as life-threatening organ dysfunction resulting from a dysregulated host response to infection. Due to relevant diagnostic limitations, microbial detection has not become an obligatory part of recent sepsis definitions [2]. Besides viruses, fungi, and parasites, sepsis-inducing infections are primarily caused by bacteria. In parallel and complementary to focus control measures, current sepsis guidelines therefore recommend an earliest possible empiric antibiotic therapy (preferably within 1 h) following sepsis diagnosis [3, 4]. Up to now, culture-based diagnostic procedures (e.g., blood cultures) are defined as diagnostic gold standard, although they are associated with relevant limitations (such as high time requirements, low sensitivity due to concomitant antibiotic therapy or being susceptible to microbial contaminations) [3–7]. Accordingly, septic patients are frequently confronted with an antimicrobial overtreatment, resulting in an increased selection of multi-drug resistant pathogens. Moreover, an inadequate or prolonged use of antibiotics is associated with a high risk for antibiotics-related toxicity, leading to short as well as long-term complications (such as acute kidney injury (AKI) with a high risk for persisting dependency on renal replacement therapy (RRT)) in septic patients. Apart from its impact on the initial anti-infective treatment strategy, the use of a more targeted pathogen diagnostic may help to avoid sepsis-associated organ dysfunctions in the early disease course and has a cross-sectoral influence on aftercare measures of affected patients [8]. The authors’ previous work suggests that next generation sequencing (NGS)-based diagnostics for pathogen identification might be a promising alternative due to its higher specificity and sensitivity compared to culture-based methods in bloodstream infections [9–11]. However, a head-to-head clinical study comparing the efficacy of this new NGS-based approach (as part of a comprehensive diagnostic workup in patients with suspected or proven sepsis/septic shock) with standard-of-care microbiological analyses is lacking. The aim of the here presented randomized, controlled, interventional, open-label, multicenter trial is therefore to characterize the effect of the combination of NGS-based digital precision diagnostics with culture-based standard diagnostics compared to solely standard-of-care microbiological analyses in the clinical picture of sepsis/septic shock.

## Methods

### Aim, design, and study setting

The primary objective of *DigiSep* is to investigate whether the so-called DOOR-RADAR (Desirability of Outcome Ranking/Response Adjusted for Duration of Antibiotic Risk) score can be significantly improved by application of an additional NGS-based diagnostic concept. The study is a randomized, controlled, interventional, open-label, multicenter trial on medical as well as surgical intensive care units (ICUs) of maximum care hospitals throughout the *Translational Intensive Care Research Network on Organ Dysfunction* (TIFOnet) in Germany. Coordinating center of the study is the Department of Anesthesiology and Intensive Care Medicine, University Hospital Essen. Noscendo GmbH, Duisburg, is responsible for NGS-based measurements in plasma samples of septic patients. Optional expert consultations are provided by experienced infectiologists of the Department of Infectious Diseases, University Hospital Essen. Project management is performed by the Coordination Centre for Clinical Trials (KKS), University of Heidelberg. Data management and statistical analysis are provided by the Institute for Medical Biometry (IMBI), University of Heidelberg. Statutory health insurance data will be provided by three different German statutory health insurers (AOK Rheinland-Hamburg, BARMER, Techniker Krankenkasse). Health economic analyses will be performed by the chair of Health Economics and Health Care Management, Bielefeld University. The study protocol follows the Standard Protocol Items: Recommendations for Interventional Trials (SPIRIT) guidelines (Supplemental File 1).

### Characteristics of participants

Patients with sepsis or septic shock according to current sepsis definitions (Sepsis-3) [2] with a sepsis onset < 24 h are eligible for study inclusion, independent of their insurance allegiance. A summary of all inclusion and exclusion criteria for participants is given in Table 1. The data of all these patients will be used for the evaluation of the study’s primary endpoint (i.e., the DOOR-RADAR score). For the analyses of several secondary endpoints, however, only patients of the three German health insurers involved in the study can be included. These are expected to be about 30% of all patients. Of note, also with the expected reduced number of patients (i.e., with about 135 patients), these secondary outcomes are sufficiently powered.

**Table 1 Tab1:** Inclusion and exclusion criteria of *DigiSep*-trial

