### Sample size calculation

For sample size calculation, a sophisticated secondary outcome analysis of the following four large sepsis studies of the SepNet Study Group (VISEP [15], MAXSEP [16], HYPRESS [17], and SISPCT [18]) was performed, in which the above described OCO-groups were represented as follows: OCO 1: 33%, OCO 2: 3%, OCO 3: 22%, OCO 4: 14%, and OCO 5: 28%. It is assumed that the anti-infective treatment period in OCO 1 and OCO 2 is 7 days in average, whereas it is prolonged up to 15 days (with a standard deviation of 10 days) in average in OCO 3 and OCO 4. Based on the assumption that the OCO group can be improved by at least 2 stages in 42% of IG patients in parallel to a shortening of the anti-infective treatment by 2 days, this would result in a power of 90% with 180 patients in each of the two study groups (CG, IG), provided that an IG patient has a lower DOOR/RADAR score as compared to a CG patient with a relative effect of *p* = 0.6. Including an additional drop-out rate of 12.5% (and considering these patients as OCO 5) would finally result in an overall sample size of 410 patients (CG: *n* = 205/IG: *n* = 205).

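### The insurer subset is put at about 135 patients where 30% of 410 is 123, and its claim of sufficient power fails at the only effect size that the article states

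*Protocol article*

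**What the plan says.** The section Characteristics of participants in the protocol article limits part of the analysis to a subset: "For the analyses of several secondary endpoints, however, only patients of the three German health insurers involved in the study can be included". On its size it says "These are expected to be about 30% of all patients", and it then adds that "also with the expected reduced number of patients (i.e., with about 135 patients), these secondary outcomes are sufficiently powered".

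The section Sample size calculation arrives at an "overall sample size of 410 patients", 205 per arm. The basis is the primary endpoint alone: "this would result in a power of 90% with 180 patients in each of the two study groups", provided that a patient in the intervention group "has a lower DOOR/RADAR score as compared to a CG patient with a relative effect of *p* = 0.6". A drop-out allowance of 12.5% is then added.

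Table 2 shows which outcomes depend wholly on the subset. Resource utilization, incapacity to work and direct medical costs list statutory health insurance data as their only source. Long-term mortality, hospital length of stay and cumulative need for anti-infective drugs also list the eCRF, and quality of life comes from a questionnaire given to all participants. Under Statistical methods, secondary endpoints are to be reported descriptively, with 95% confidence intervals and descriptive p values.

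**The concern.** Two things in the same place do not fit the rest of the article. The subset size does not follow from the stated share and the stated total, and the mismatch makes the subset look larger. That size then serves as the footing for a positive statement about power. The article shows no calculation for it, and it sits uneasily with a primary endpoint that is planned on 360 evaluable patients.

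Cost-effectiveness is a declared aim, in the Abstract and again under Secondary outcomes, and the three outcomes that rest only on insurance data carry much of it. A published assurance of sufficient power affects how a result showing no clear difference in costs or resource use would be read. A reader who trusts it may give such a result more weight than about 60 patients per arm can bear.

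**Working it through.** **Inputs.** From Characteristics of participants: a share of about 30% and a subset of about 135. From Sample size calculation: 410 in total, 180 per arm for 90% power, relative effect 0.6, drop-out 12.5%. From Statistical methods: Mann-Whitney U test for the primary hypothesis, significance level 0.05. From Randomization process and interventions: 1:1 allocation. Sidedness is not stated; two-sided is assumed, for the reason given in step 1.

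**Step 1: reproduce the plan's own calculation.** Noether's formula for the Mann-Whitney test with equal allocation is

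N = (z(1−α/2) + z(power))² / [3 (p − 0.5)²].

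With z values 1.960 and 1.282 and p = 0.6, N = 10.507 / 0.03 = 350.2, or 176 per arm against the stated 180. At N = 360 the power is 90.8%. A one-sided test would need only 143 per arm, which does not match, so two-sided is the reading that fits. For drop-out, 360 / 0.875 is 412 after rounding up, against the stated 410. The primary calculation is reproduced closely enough to use the same method below.

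**Step 2: subset size.**

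- 0.30 × 410 = 123, about 61 per arm.
- 135 / 410 = 32.9%.
- 135 / 0.30 = 450, a total that appears nowhere in the article.
- 0.30 × 360 evaluable patients = 108, further from 135.

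**Step 3: power in the subset at relative effect 0.6.** Carrying this effect and a rank test over to the insurer outcomes is an assumption, because the article states both only for the primary endpoint. Power = Φ(√(3N) × 0.1 − 1.96).

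| N | √(3N) × 0.1 | Power, two-sided 5% | Power, one-sided 5% |
|---|---|---|---|
| 108 | 1.800 | 43.6% | 56% |
| 123 | 1.921 | 48.4% | 61% |
| 135 | 2.012 | 52.1% | 64% |

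A simulation with normally distributed outcomes shifted to give p = 0.6 agrees: about 47% power with 61 per arm and 50% with 67 per arm.

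**Step 4: relative effect needed.** p = 0.5 + (1.960 + z(power)) / √(3N).

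| N | 80% power | 90% power |
|---|---|---|
| 123 | 0.5 + 2.802 / 19.21 = 0.646 | 0.5 + 3.242 / 19.21 = 0.669 |
| 135 | 0.5 + 2.802 / 20.12 = 0.639 | 0.5 + 3.242 / 20.12 = 0.661 |

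On the scale of distance from 0.5, 80% power needs 0.14 to 0.15 where the primary endpoint was planned on 0.10.

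**The case against.** The best defence is that the comparison borrows its effect. The 0.6 was set for DOOR-RADAR, and the Mann-Whitney test is named only for the primary hypothesis. Nothing in the article says that effects on costs or sick leave should be of that size, and with a relative effect of about 0.65 or more the subset would reach 80% power. This stands. A reader might infer that the power for the cost outcomes is about 50%; the documents do not support that, because they give no expected effect for those outcomes.

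It can also be said that an article condenses a full protocol and defers detail to a separate analysis plan, so a power calculation may exist elsewhere. This stands too: the absence of a calculation here is not proof that there is none, and leaving it out would not by itself be a fault. But the article goes further and asserts the result, on a subset size that does not follow from its own total.

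The numerical gap is small. Both figures are qualified as approximate, the difference is 12 patients, and it moves the power in step 3 by less than four points. On its own it would be a minor correction.

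The descriptive p values and the 95% confidence intervals already planned limit the harm from a misread null result. This lowers the severity, but it fits an exploratory label better than a claim of sufficient power.

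Two further arguments should not be made. A reader might infer that the 28% share of deaths assumed in the sample size section shrinks the subset further, but patients who die still generate inpatient costs and resource use. Nor does the article state a working-age restriction for incapacity to work. Likewise, turning the detectable effect into about 0.5 standard deviations needs roughly normal data, and the article says nothing about how costs are distributed.

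**Conclusion.** The point holds in limited form. The subset size is wrong as written: the stated share and total give 123 patients, not 135. The statement of sufficient power has no basis shown in the article, and it fails at the only effect size given there, with 48% power at 123 patients and 52% at 135 for a two-sided 5% rank test. Accepting 135 or testing one-sided does not bring the power to 80%.

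The power figures rest on three assumptions: relative effect 0.6 is carried over from DOOR-RADAR, a rank test is used, and the test is two-sided. They show that the claim depends on effects clearly larger than the one planned for the primary endpoint, not what the power for any particular insurer outcome is. The full force falls on resource utilization, incapacity to work and direct medical costs. Severity is moderate, because these are secondary outcomes reported descriptively and the primary analysis and sample size are untouched.

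**What to change.** In Characteristics of participants, restate the subset as about 123 patients (about 61 per arm), or correct the 30% share if 135 is the figure the sponsor expects and can justify.

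Then replace the statement of sufficient power in one of two ways:

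- for each outcome that rests only on insurance data, give the assumed effect and variability, the test and the resulting power; or
- give the detectable effect (a relative effect of about 0.65 at 80% power for a two-sided 5% rank test with 123 patients) and label these analyses exploratory, in line with the descriptive p values under Statistical methods.

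If a calculation already exists in the full protocol or the analysis plan, the first option amounts to citing it, after checking it against the corrected subset size. The cost is a change of wording and a less favourable stated figure. Design, recruitment and the primary analysis stay as they are.

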**Inclusion criteria**	
Age ≥ 18 years	
Informed consent	
Sepsis *or* septic shock (with an onset ≤ 24 h)	
**Exclusion criteria**	
Age < 18 years	
Refusal to give consent	
Patient will probably be discharged from the ICU/IMC within the first 72 h following inclusion	
Palliative treatment intent	
Clinician is not committed to aggressive treatment	
Death is deemed imminent and inevitable	
Patients who had previously been included but are readmitted to the ICU/IMC during the same hospitalization will not be included a second time.	

Abbreviations: *ICU* intensive care unit; *IMC* intermediate care unit

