### Randomization process and interventions

Eligible patients will be randomized (1:1) into one of the two different study arms (CG, control group/IG, intervention group) using block randomization with randomized block length. The randomization is done stratified by study center using an internet-based tool (URL: www.randomizer.at). The randomization is blinded for the patient, blinding of the attended physician is not possible. All included patients will be treated according to current sepsis guidelines [3, 4]. Pathogen diagnostics in patients of the CG will be done with standard-of-care microbiological analyses followed by optional expert consultations, whereas in patients of the IG, a comprehensive concept of digital precision diagnostics (including NGS-based diagnostics, standard-of-care microbiological analyses, and optional expert consultations) will be provided.

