### Outcomes

#### Primary outcomes

*DigiSep* primarily evaluates whether the so-called DOOR-RADAR (Desirability of Outcome Ranking/Response Adjusted for Duration of Antibiotic Risk) score can be significantly improved by application of an additional NGS-based diagnostic concept [14] (Table 2).

**Table 2 Tab2:** Primary and secondary outcomes of *DigiSep*-trial

Outcomes	Data source	Timepoint/frame
Primary outcomes		
DOOR/RADAR score	eCRF	28 days
Secondary outcomes		
Long term mortality	Statutory health insurance data, eCRF	90, 180 days
Degree of organ dysfunction/failure: • Duration of mechanical ventilation • Length of time until shock resolution • Ongoing RRT-dependency	eCRF	28, 90, 180 days
Hospital length of stay	Statutory health insurance data, eCRF	28, 90, 180 days
Cumulative need for anti-infective drugs	Statutory health insurance data, eCRF	28, 90, 180 days
Beginning of a targeted anti-infective treatment regimen	eCRF	28 days
Resource utilization (outpatient and inpatient)	Statutory health insurance data	28, 90, 180 days
Duration and costs of incapacity to work	Statutory health insurance data	28, 90, 180 days
Direct medical costs (outpatient and inpatient)	Statutory health insurance data	28, 90, 180 days
Quality-of-life (QoL)	VR-36 questionnaire	0, 90, 180 days

Abbreviations: *RRT* renal replacement therapy; *QoL* quality of life; *eCRF* electronic case report from; *DOOR/RADAR score* Desirability of Outcome Ranking/Response Adjusted for Duration of Antibiotic Risk score

The DOOR-RADAR score represents a combined clinical endpoint. While the DOOR component reflects the overall clinical outcome (OCO) consisting of intensive/intermediate care unit length of stay (ICU/IMC-LOS), mortality, and RRT-dependent AKI, the RADAR component reflects the duration of anti-infective treatment. Both components are combined to yield the DOOR-RADAR score, which is a numerical value and calculated as follows:
$$ \mathrm{DOOR}-\mathrm{RADAR}\ \mathrm{score}\ \left\{\begin{array}{c}=\mathrm{OCO}+\left[\frac{\mathrm{number}\ \mathrm{of}\ \mathrm{days}\ \mathrm{with}\ \mathrm{anti}-\mathrm{infective}\ \mathrm{treatment}\kern0.5em }{\max .\kern0.5em \mathrm{number}\ \mathrm{of}\ \mathrm{days}\ \mathrm{with}\ \mathrm{anti}-\mathrm{infective}\ \mathrm{treatment}\kern0.5em +1\ \mathrm{day}}\right],\mathrm{if}\ \mathrm{OCO}\le 4\\ {}=5\kern28em ,\mathrm{if}\ \mathrm{OCO}=5\end{array}\right. $$

with the OCO being calculated as

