### Recruitment process

All adult patients (≥ 18 years) in the participating centers with suspected or proven sepsis/septic shock will be considered for inclusion in this study.

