### Statistical methods

The primary hypothesis will be analyzed using Mann-Whitney *U* test. Primary analysis will include all randomized patients (intention to treat (ITT)-population). Although DOOR/RADAR score values can be calculated reliably, any missing data will be replaced with multiple imputation methods [20]. The imputation model will be based on the variables age, SOFA score at sepsis onset, and survival and furthermore assumes that missing values of the primary endpoint are “missing at random”. Accordingly, missing values can be estimated by relevant co-variables in the imputation model. In order to review the assumptions of the imputation model, sensitivity analyses as well as “best case” and “worst case” scenarios will be performed. Moreover, these cases will be analyzed without the missing variables (complete case analysis). The primary endpoint will additionally be analyzed in a dichotomous way (good vs. bad outcome: e.g., OCO 1 versus OCO 2-5) using a logistic regression model, including group membership (CG, IG) and additional confounders (e.g., age, sex, SOFA score, comorbidities) as co-variates. The primary as well as all secondary endpoints will be presented using descriptive statistical methods. Moreover, 95% confidence intervals as well as descriptive *p* values for the effect estimates will be reported. In addition, mortality at 90 and 180 days will be evaluated using methods for survival-time analyses (Kaplan-Meier, Cox-proportional-Hazards-Regression). Wherever possible, graphs are used for visualization. All statistical tests will be performed using SAS (SAS Institute, Cary, NC). A *p* value of < 0.05 will be considered statistically significant. Detailed information of all statistical methods will be summarized and refined in a detailed statistical analytic plan (SAP).

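### The bar on re-inclusion stops at the same hospitalization, so a patient with a new sepsis episode in a later admission can be randomised again during the first inclusion's 180-day follow-up

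*Protocol article*

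**What the plan says.** Re-inclusion is addressed once, in the last exclusion criterion of Table 1 (protocol article, Characteristics of participants): "Patients who had previously been included but are readmitted to the ICU/IMC during the same hospitalization will not be included a second time". Two conditions must hold together: a readmission to the ICU/IMC, and the same hospitalization.

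No other section narrows entry further on this point:

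- **Entry event (Table 1, inclusion criteria).** Sepsis or septic shock "with an onset ≤ 24 h", with no requirement that it be the patient's first episode.
- **Recruitment process.** The pool is broad: "All adult patients (≥ 18 years) in the participating centers with suspected or proven sepsis/septic shock will be considered for inclusion in this study". Earlier participation is not mentioned.
- **Randomization process and interventions.** "Eligible patients will be randomized (1:1) into one of the two different study arms", and "The randomization is done stratified by study center using an internet-based tool". Nothing ties a second allocation to the first.
- **Statistical methods.** "Primary analysis will include all randomized patients (intention to treat (ITT)-population". The primary test is the Mann-Whitney U test. Mortality at 90 and 180 days is analysed by Kaplan-Meier and Cox regression.

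The primary endpoint is read at 28 days. Table 2 sets mortality at 90 and 180 days, most other secondary outcomes at 28, 90 and 180 days, and quality of life at 0, 90 and 180 days.

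**The concern.** Sepsis can recur, and follow-up is long compared with a hospital stay. By confining the bar to one hospitalization, the criterion leaves a patient who comes back from home eligible again, at the same centre or another one. If that happens within 180 days of the first onset, the two observation periods overlap.

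Three things are then at stake.

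- **Independence.** The Mann-Whitney test and the Cox model assume independent units, and two records from one patient are correlated.
- **Shared events.** One death, or the same hospital days, anti-infective days, costs or quality-of-life measurements, can be attributed to two records, possibly in opposite arms.
- **Arm separation.** A control patient re-randomised to the intervention receives NGS-guided care inside the control record's follow-up. In the reverse order, the patient enters the control arm with NGS results already reported to a physician.

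An analysis plan can decide which record to use, but it cannot undo a second allocation. This therefore belongs in the eligibility criteria.

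**Working it through.** **1. The plan's own sample size.** Inputs from Sample size calculation: relative effect 0.6, power 90%, 180 per arm, drop-out 12.5%, total 410. Statistical methods gives a 0.05 significance level; two-sided is assumed.

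Noether's formula: N = (z₀.₉₇₅ + z₀.₉₀)² / [12 × 0.25 × (p − 0.5)²] = (1.960 + 1.282)² / (3 × 0.01) = 350.2, or 176 per arm against 180 stated.

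Power at 360: Φ(√(3 × 360) × 0.1 − 1.960) = 90.8%. With drop-out: 180 / 0.875 = 205.7 against 205 stated. The plan's figures reproduce, and they count 410 distinct patients. A once-only rule leaves them unchanged.

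**2. When two records overlap.** Let the second onset fall s days after the first. For a window of W days, the overlap is W − s if s < W, otherwise none. A death t days after the second onset counts in both records only if s + t ≤ W. For s = 60:

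- 28-day primary endpoint: no overlap.
- 90 days: 90 − 60 = 30 days of overlap.
- 180 days: 180 − 60 = 120 days of overlap.
- Death at t = 40 (day 100 of the first record): at 90 days it counts only in the second record; at 180 days it counts in both.
- Death at t = 130 (day 190 of the first record): at 180 days it counts only in the second record.

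The DOOR-RADAR score is shared only if s < 28. By the later-admission route, that means discharge, a new admission and a new onset all within 28 days.

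**3. Number of records.** The document gives no recurrence rate, so 1–5% of randomisations is assumed: 0.01 × 410 ≈ 4 to 0.05 × 410 ≈ 20. With 1:1 allocation, about half (2–10) would place one patient in both arms. Insurer-based outcomes such as costs cover about 30% of patients, so about 0.3 × 4 ≈ 1 to 0.3 × 20 = 6 of these records.

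**4. Effect on the primary test.** For a lower bound on power, suppose repeat records carry no new information: Φ(√(3 × N(1 − f)) × 0.1 − 1.960), where f is the repeat fraction. At f = 5% and N = 410: Φ(√(3 × 389.5) × 0.1 − 1.960) = Φ(1.458) = 92.8%.

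For type I error, m repeat pairs with within-patient correlation ρ multiply the variance of the arm difference by 1 + 2mρ/410 if all fall in the same arm, and by 1 − 2mρ/410 if all fall in opposite arms. With m = 20 and ρ = 1 these are 1.0976 and 0.9024. The actual level is 2[1 − Φ(1.960/√factor)].

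| Repeats | Power, N = 410 | Power, N = 360 | Level, all same arm (ρ = 1) | Level, all opposite arms (ρ = 1) |
|---|---|---|---|---|
| 0% | 93.9% | 90.8% | 0.0500 | 0.0500 |
| 1% (m = 4) | 93.7% | 90.5% | 0.0522 | 0.0478 |
| 2% (m = 8) | 93.5% | 90.2% | 0.0545 | 0.0456 |
| 5% (m = 20) | 92.8% | 89.3% | 0.0614 | 0.0391 |

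The last two columns are extremes. Under random 1:1 re-allocation, same-arm and opposite-arm pairs largely cancel.

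**The case against.** Several points on the other side are sound.

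- **Same ICU stay.** A reader might infer that a patient with a new episode in the same ICU stay could also be randomised again, because that patient is not readmitted. This is too literal. A rule that bars someone who left the unit and came back almost certainly means to bar someone who never left. Sample collection and sample handling also allows further NGS sampling after baseline within the existing inclusion. The wording does not expressly cover the case, but the intent is probably to bar it.
- **Analysis set.** A reader might infer that the intention-to-treat set takes every randomisation. Statistical methods says patients, and the sample size is counted in patients. Handling of repeat records may be in the analysis plan, which is not shown.
- **Deaths.** A reader might infer that every death after a second inclusion is counted twice. Step 2 shows that this holds only when the death lies inside both windows.
- **Condensed source.** Table 1 is described as a summary, and the full protocol may state that each patient is included once.
- **Deliberate choice.** Admitting a later, distinct episode can be intended.

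What stands is the later-admission route. The article states the criterion itself and limits it to one hospitalization, and no section shown gives a once-only rule. If re-entry is intended, the article does not say so or address the overlap with the first follow-up.

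**Conclusion.** The point holds for later hospitalizations and is minor. As written, Table 1 lets a patient be randomised a second time while the first inclusion is still in its 180-day follow-up, possibly to the other arm.

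The case rests on keeping one record per patient and keeping the arms separate, chiefly for the 90- and 180-day outcomes. It does not rest on lost power. A reader might infer that the primary analysis is compromised, but the figures do not support that. At an assumed 1–5% of repeats, power falls by at most about 1.5 percentage points (90.8% to 89.3% with N = 360). The level moves to 0.061 or 0.039 only if ρ = 1 and every repeat falls on the same side. Shared primary-endpoint days also need a second onset within 28 days, which should be rare.

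The conclusion assumes that the full protocol and screening forms carry the same wording as the article. The repeat rate is an assumption and cannot be derived from the document.

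**What to change.** Replace the last exclusion criterion in Table 1 with: any previous randomisation in DigiSep, irrespective of ICU/IMC stay, hospitalization or centre. Add that a further sepsis episode after randomisation is followed as part of the first inclusion. This also settles the same-stay case.

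If repeat inclusions have already occurred, state before analysis that only the first randomisation per patient is analysed and that later episodes count as its follow-up.

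The cost is one line in Table 1 and in the screening checklist, a check for earlier randomisation across centres, and a handful of repeat inclusions lost. The planned 410 patients do not change.
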